### Gaps in knowledge

To date, there have been three published randomised trials in which researchers investigated whether early screening and treatment of young females would reduce the incidence of PID over a 12-month period [10–12]. The most recent and methodologically sound study, the prevention of pelvic infection (POPI) trial conducted in England, yielded inconclusive results. Moreover, most PID cases occurred in women who had a negative test result for Ct at baseline, raising the question of the optimal frequency of testing [12].

Key characteristics of Ct infection natural history (i.e., rate and timing of progression of lower genital tract infection to PID) are not sufficiently documented. Yet, accurate estimates of these characteristics are needed to better anticipate the benefit of early and systematic screening for infection. Further, the average duration of Ct infection in the absence of treatment is not well established and could possibly be 1 year or longer [13]. Finally, reinfection is common following therapy (10–20% patients within 12 months) [14, 15], thus raising questions about host immune response and the relevance of and time to retesting.

Inter-individual variations in host immune response may explain why some women develop complications such as PID after Ct infections and others do not. Among various genetic markers, single-nucleotide polymorphisms (SNPs) have been shown to be related to the development of late complications of Ct infections in women [16, 17]. This approach could be relevant to identifying women at risk for PID and tubal pathology and adapting treatment and follow-up for these women. In summary, there is a need to evaluate the efficacy of early screening for prevention of PID and to better understand the natural history of Ct infection and progression to PID in order to develop efficient screening programmes in France.

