#### Follow-up

All participants will self-collect vaginal samples in the privacy of their home at months 6, 12 and 18. A kit including detailed self-sampling instructions will be mailed to them a few days prior to each due date. Participants will mail the sample back to the CNR and complete an electronic self-administered questionnaire about their number of sexual partners, condom use, symptoms such as abnormal vaginal discharge or pelvic pain, additional testing since their previous sample, medical visits and antibiotic use (for Ct or other infections).

Participants with a positive test result for Ct at baseline or months 6, 12 or 18 in the intervention group will be referred to their physician or the nearest STI clinic for treatment. Of note, current recommendations for uncomplicated infections include a single-dose therapy of azithromycin (1 g) or a 7-day course of doxycycline [18].

The physician collecting clinical data upon examination will fill out a specific form, handed out by the participant together with a prepaid envelope, on clinical findings, as well as treatment initiated, results of additional tests or ultrasound (if any), and information regarding whether a partner was treated (if available). These data will be received at the UHS and entered by a trained clinical research assistant on the Cleanweb® platform.

At any moment during follow-up, all participants will be asked to complete a short, self-administered questionnaire online each time they feel unusual lower abdominal pain. A contact will be made with the participant 24–48 h after completion of this short pelvic pain questionnaire to encourage the participant to visit the closest participating gynaecology emergency department (GED), where they will be evaluated for PID according to current national recommendations by the Collège National des Gynécologues et Obstétriciens Français [19]. Data from these visits to the GED will be made available to the trained clinical research assistant, who will collect them using a standardised clinical research form and enter the clinical data on the Cleanweb® platform.

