#### Secondary endpoints

The following secondary endpoints will be measured:Prevalence of Ct infection in participants at baseline (intervention and control groups)Incidence of first Ct infection in participants with a negative Ct test result at baseline (intervention and control groups)Incidence of first PID (intervention and control groups)Duration of Ct infection (6 or 12 months or over 18 months because the time window between each assessment is 6 months); proportion of infections associated with a diagnosis of PID (whether at a previous visit or concurrently) and time to development of PID since Ct infection; proportion of spontaneous Ct infection resolution (control group), defined as a Ct-negative sample after one or more Ct-positive samplesIncidence of reinfections (intervention and control groups); an algorithm to differentiate between Ct reinfection, treatment failure and persistent infection [21] will be developed on the basis of typing (as described below in laboratory analyses), treatment, partner notification and change of partner

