### Sample size

The cumulative number of PID cases (from baseline to up to 18 months) was estimated in each group, assuming no natural clearance of Ct infection in the absence of treatment, because Ct infection is mostly asymptomatic and the follow-up relatively short in comparison to infection duration, which is most likely > 1 year [13]; 100% treatment efficacy to clear Ct and PID; and an average 3-month lag between Ct acquisition and PID onset [27, 28]. The same number of Ct-infected and PID cases is expected in the two groups at baseline, assuming that observed Ct infections at baseline have been prevalent for an average of 9 months (hence a PID cumulative incidence over 6 months).

Assuming a 5% yearly incidence of Ct infection [14] and a 1% yearly incidence of PID among Ct-negative young women, we calculated that a sample size of 2000 participants in each group would allow us to detect a 0.54 relative risk (RR) between the intervention and control groups with a 5% one-sided type I error rate and 80% power, assuming either 5% Ct prevalence at baseline [12] and 12% PID incidence among Ct-positive participants or 7% Ct prevalence at baseline [29] and 10% PID incidence among Ct-positive participants [12], and accounting for a 10% attrition rate. Therefore, 4000 sexually experienced female students aged 18 to 24 years participating in the i-Share French student cohort will be enrolled.

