### Statistical analyses

For the primary analysis, we will calculate the cumulative incidences of developing PID over 24 months in both groups and estimate the RR of developing PID as the ratio of these incidences (intention-to-treat analysis). We will consider probable and confirmed PID together first and conduct confirmatory analysis restricted to confirmed PID only.

For comparison with previous trials, we will further stratify our RR analysis on baseline status of Ct infection. We will also conduct an exploratory Cox regression analysis to adjust the RR of developing PID for other baseline characteristics of the participants. Missing data imputation will be considered for participants’ characteristics (excluding Ct and PID status) when missing values exceed 10%.

As secondary analyses, we will determine the following:Annual incidence of Ct infection based on the first recorded Ct infection among participants Ct-negative at baseline in both groupsAmong participants in the control group with incident Ct infection (participants Ct-negative at baseline), proportions (and 95% CIs) of Ct infections with spontaneous resolution and of Ct infections evolving towards PID; estimation of the duration of Ct infection (from Ct detection to clearance) and time to develop PID (time between incident Ct infection and incident PID, defined as from 3 months before Ct detection because time windows correspond to 6 months, to the onset of PID symptoms)Among participants in both groups who have cleared Ct infection at least once, incidence of Ct reinfection and comparison between the treated (intervention) and untreated (control) groupsAmong participants in the control group, exploratory logistic regression to assess whether 50 immunogenetic biomarkers can predict Ct persistence and occurrence of PID

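### Annual Ct incidence based on first recorded infections at 6-monthly swabs misses infections that clear between swabs: roughly 5–21% too low if durations are exponential with mean 5 down to 1 year

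*Protocol article*

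**What the plan says.** The endpoint, listed under Secondary endpoints for both groups, is "Incidence of first Ct infection in participants with a negative Ct test result at baseline". Statistical analyses makes it operational as "Annual incidence of Ct infection based on the first recorded Ct infection" among baseline-negative participants in both groups. Under Follow-up, "All participants will self-collect vaginal samples in the privacy of their home at months 6, 12 and 18", so with the month-0 swab there are three 6-month gaps.

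On how long an untreated infection lasts, Gaps in knowledge says that "the average duration of Ct infection in the absence of treatment is not well established and could possibly be 1 year or longer". Sample size describes "the follow-up relatively short in comparison to infection duration, which is most likely > 1 year" and works by "assuming no natural clearance of Ct infection in the absence of treatment", but that premise serves the projection of pelvic inflammatory disease (PID) cases. Secondary endpoints and Statistical analyses both make spontaneous resolution and duration of infection in the control group study results.

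Follow-up also provides for questionnaires on tests done elsewhere, medical visits and antibiotic use, and for forms completed by treating physicians.

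**The concern.** A rate built on first detections equals the acquisition rate only if no infection comes and goes within a gap, or if those that do are picked up some other way. The trial expects clearance and sets out to measure it, yet the described incidence analysis makes no allowance for it. The neighbouring analysis of time to PID does take the 6-month window into account, by dating infection three months before detection. That settles when a detected infection began. It does not recover infections that were never detected.

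The error runs in one direction and does not shrink with sample size. Ct incidence belongs to the first-listed secondary objective, and the article presents the trial as a source of natural-history data for decisions on screening. An understated incidence with an interval that reflects only sampling error would carry over into such work.

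**Working it through.** The plan states no precision or target for Ct incidence, so it has no figure of its own to reproduce. The 2000 per group is derived for PID and does not bear on this point.

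**Inputs**
- Acquisition rate λ = 0.05 per year (Sample size: "Assuming a 5% yearly incidence of Ct infection").
- Swabs at 0, 0.5, 1.0 and 1.5 years (Follow-up).
- Baseline-negative women followed, with 5% prevalence and 10% attrition from Sample size: 4000 × 0.95 × 0.90 = 3,420 pooled, 1,710 per arm. Using the plan's alternative 7% prevalence changes the half-widths below by at most 0.2 percentage points.
- Clearance rate μ = 1/D, with D the mean duration. The exponential form and the values of D are assumptions. The documents give no distribution and no mean, only one year or longer.
- Outside diagnoses are not counted in steps 1 to 3.

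**Step 1: share of new infections still present at the next swab.** For acquisition spread evenly over half a year, the share is (1 − e^(−0.5/D)) / (0.5/D).
- D = 5: 0.0952/0.1 = 0.952
- D = 2: 0.2212/0.25 = 0.885
- D = 1: 0.3935/0.5 = 0.787

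**Step 2: recorded incidence over the three gaps.** The probability that a woman negative at one swab is positive at the next is p = λ/(λ+μ) × (1 − e^(−0.5(λ+μ))). For D = 2 this is 0.0909 × 0.2404 = 0.02186. Expected first detections are 3,420 × (1 − (1 − p)³), which for D = 2 is 219.4. Person-time runs to the midpoint of the detecting gap, or to 1.5 years if never detected; for D = 2 this is 4,964 years. The recorded rate is 219.4/4,964 = 0.0442 per year, and 0.0442/0.05 = 0.884.

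**Step 3: coverage.** The recorded count is Poisson with the expected value above. An exact 95% Poisson interval covers if it contains λ × person-time, the count that the true rate would give (for D = 2, 0.05 × 4,964 = 248.2). The relative half-width is 1.96/√(expected count).

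| Mean duration D (years) | p | Expected recorded, pooled | Recorded/true | Shortfall | 95% half-width, pooled | Coverage, pooled | Coverage, one arm |
|---|---|---|---|---|---|---|---|
| 5 | 0.02350 | 235.5 | 0.951 | 4.9% | 12.8% | 89% | 93% |
| 3 | 0.02275 | 228.1 | 0.920 | 8.0% | 13.0% | 78% | 86% |
| 2 | 0.02186 | 219.4 | 0.884 | 11.6% | 13.2% | 55% | 75% |
| 1.5 | 0.02101 | 211.1 | 0.849 | 15.1% | 13.5% | 33% | 61% |
| 1 | 0.01945 | 195.7 | 0.786 | 21.4% | 14.0% | 5% | 31% |

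With no clearance the same calculation gives a ratio of 1.000 and coverage of 95%, so the shortfall comes from clearance and not from the person-time rule. A simulation of 2,000,000 women agreed (shortfall 11.7% at D = 2 and 21.4% at D = 1).

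**Step 4: what would reduce it.** If every infection lasts more than six months, none is lost and the shortfall is nil. If half of the infections lost between swabs were recorded through outside testing (an assumption), simulation gives a shortfall of about 6% at D = 2 and 10% at D = 1.

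**The case against.** The strongest reply is that the text speaks of a recorded infection, not of a positive trial swab. Outside tests and treatment are collected, participants are told they may be tested whenever they wish, and nothing says that such diagnoses are excluded. This stands in part. Counting them would shrink the shortfall, but it would not be expected to remove it, because the Background puts 70–80% of lower-tract infections as asymptomatic. The article also does not say whether they count.

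Second, the size depends on a duration distribution that the documents do not supply. This stands. A reader might infer a fixed understatement of 12–22%, larger than the sampling error. The documents do not support that: it needs exponential durations with mean 2 down to 1 year, and one year is the edge of what they expect. Against the pooled 95% half-width, an 11.6% shortfall at two years does not exceed 13.2%. Within one arm the half-width is 18–20%, so the shortfall exceeds it only for mean durations close to one year.

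Third, a reader might infer that the plan treats infections as unable to clear. It does not: that premise is confined to the PID sample size, and clearance is itself an endpoint.

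Fourth, the exact rate estimator may be set out in an analysis plan that is not shown. That is a reason for modest severity. The article nevertheless names the basis of the estimate, and the analyses it describes do not adjust for missed infections.

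Finally, a two-state model also leans on a constant clearance rate, so it exchanges one assumption for another. That also stands, and it limits how the corrected figure should be presented.

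**Conclusion.** The point holds, with its size conditional. Incidence based on first recorded infections under 6-monthly swabbing is biased downward wherever some infections clear within a gap and are not diagnosed elsewhere. At 5% yearly incidence with exponential durations, the understatement is roughly 5% at a mean of five years, 12% at two and 21% at one. With both arms pooled this is comparable to the sampling error: it does modest harm to the interval at five years, leaves it covering the truth little more than half the time at two, and makes it almost always miss at one. A single arm fares better only because its interval is wider. Longer or less variable durations, or outside diagnoses, bring the bias down, to nil in the limit. The endpoint is secondary and descriptive, and neither the PID comparison nor its sample size depends on it.

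**What to change.** Three changes to the analysis text, none needing new data:

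1. Report the crude figure under a name that says what it is: the rate of infections detected under 6-monthly testing.
2. State that Ct diagnoses made outside the trial, already captured by questionnaire and physician form, count as recorded infections, and how they are dated.
3. Add, as a corrected or sensitivity estimate, a two-state (uninfected/infected) continuous-time panel model fitted to the whole swab sequence. It should estimate acquisition and clearance together, with treatment as a time-dependent covariate so that treated clearance is not read as spontaneous.

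The cost is a few sentences and one standard model. The model relies on roughly constant rates between swabs, so clearance within six months is partly extrapolated, and its interval will be wider than the crude one. It should therefore be shown beside the crude rate with that assumption stated, not in place of it.

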**Discussion:**

This trial is expected to largely contribute to the development of recommendations for Ct screening in young women in France to prevent PID and related complications. It is part of a comprehensive approach to gathering data to facilitate decision-making regarding optimal strategies for Ct infection control. The control group of this randomised trial, following current recommendations, will allow better documentation of the natural history of Ct infection, a prerequisite to evaluating the impact of Ct screening. Characterisation of host immunogenetics will also allow identification of women at risk for complications.

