**Fig. 3 Fig3:**
[figure not shown]
Sample flow of the i-Predict trial

After sampling, the kit will be returned to the CNR (Bordeaux, France) in a pre-addressed, prepaid envelope. At the CNR, samples will be recorded. All samples will be analysed using a commercially available, CE-marketed, transcription-mediated amplification assay (Aptima Combo 2 CT/NG; Hologic) on the automated Panther instrument (Hologic), which performs well on self-collected vaginal swabs [24]. In the intervention group, samples will be analysed upon arrival. Analysis will be deferred for the control group to after the 18-month study period, and the samples will be stored at − 80 °C immediately after being received.

To determine whether a Ct infection is persistent or new, typing methods developed in the CNR will be applied, enabling high-resolution molecular epidemiological characterisation of Ct genovars D to K: *omp1* gene PCR-restriction fragment length polymorphism [25] or *omp1* gene sequencing, followed by multiple loci variable-number tandem repeat analysis [26] in case the same genovar is identified in two samples from the same subject. The CNR will perform DNA extraction from vaginal swabs and transfer the prepared samples to the immunogenetics laboratory for SNP biomarker analyses. These will be performed using a set of over 50 SNPs already identified and validated to be predictive of tubal factor infertility susceptibility [16].

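### The control arm is expected to yield only about one to 1.7 PID events per genetic marker, too few for the planned 50-marker logistic regression to support the stated prediction claim

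*Protocol article*

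**What the plan says.** The last of the secondary analyses in Statistical analyses is restricted to the control group and is an "exploratory logistic regression to assess whether 50 immunogenetic biomarkers can predict Ct persistence and occurrence of PID". Materials/laboratory analyses says the genotyping will be done "using a set of over 50 SNPs already identified and validated to be predictive of tubal factor infertility susceptibility", so the panel is at least as large as the regression suggests and was validated for a different outcome.

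The Sample size section is built for the primary relative risk only. It sets 2000 women per arm for a relative risk of 0.54 "with a 5% one-sided type I error rate and 80% power", "accounting for a 10% attrition rate". It gives no event count for the genetic analysis.

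The abstract's Discussion states without qualification: "Characterisation of host immunogenetics will also allow identification of women at risk for complications". Expected results, in the main Discussion, names a tool for picking out women at risk as the eventual aim.

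**The concern.** The article fixes the method, the number of predictors, the population and a predictive aim. It does not set these against the number of PID cases that its own planning rates produce. With about one event per candidate predictor, an unpenalised joint model describes noise well and new women not at all. Testing markers one at a time avoids that mechanism but brings a multiplicity problem that also gives false leads.

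The population also mixes two questions. Gaps in knowledge asks why some infected women progress to PID and others do not, and persistence is defined only in women who have been infected. Yet about half of the PID events expected in the control arm do not come from Ct infection in the planning model.

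What is at stake is the claim that host genetics will identify women at risk. The comparison of screening strategies is not at stake.

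**Working it through.** **Inputs (Sample size section).** 2000 per arm; 10% attrition, so 1800 evaluable; relative risk 0.54; one-sided 5%; 80% power. Rates: "Assuming a 5% yearly incidence of Ct infection [14] and a 1% yearly incidence of PID among Ct-negative young women". Scenario A: 5% baseline prevalence, 12% PID incidence if Ct-positive. Scenario B: 7% and 10%. Lag from infection to PID: 3 months. Horizon for counting cases: 18 months. The control-arm PID risk is not printed, so it is reconstructed in two ways.

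**1. Reproduce the stated sample size and back-solve the risk.** The two-proportion formula (pooled null variance), with control risk 2.45% and intervention risk 0.54 × 2.45% = 1.32%, gives 1801 per arm. 1801 / 0.90 rounds up to 2002, against 2000 stated. Control events: 1800 × 0.0245 = 44, or 48 if a continuity correction is used.

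**2. Build the risk from the stated rates** (read as yearly). Control risk = (1 − prev) × 0.01 × T + prev × r × T + (1 − prev) × 0.05 × r × (T − 0.25)² / 2, where r is the PID rate if Ct-positive.

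| | Background | Prevalent Ct | Incident Ct | Total | Events in 1800 | From Ct |
|---|---|---|---|---|---|---|
| A, T = 1.5 | 0.01425 | 0.00900 | 0.00445 | 2.77% | 50 | 24 |
| B, T = 1.5 | 0.01395 | 0.01050 | 0.00363 | 2.81% | 51 | 25 |
| A, T = 2 | 0.01900 | 0.01200 | 0.00873 | 3.97% | 72 | 37 |
| B, T = 2 | 0.01860 | 0.01400 | 0.00712 | 3.97% | 71 | 38 |

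Other readings (background risk applied to all women, PID already present at baseline counted, incident infection placed at interval midpoints) give 49 to 59 events at 18 months. At 24 months the readings tried run from 69 to 84.

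**3. Events per marker.** 44 / 50 = 0.9; 59 / 50 = 1.2; 84 / 50 = 1.7. A panel of more than 50 markers, or the analysis of confirmed PID only, lowers these.

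**4. Joint fit when no marker matters.** Simulation with 50 independent SNPs (assumed allele frequency 0.1 to 0.5), outcome unrelated to any of them, unpenalised logistic regression:

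| Women | Events | Mean apparent AUC | AUC in new data |
|---|---|---|---|
| 1800 | 50 | 0.77 | 0.50 |
| 1800 | 60 | 0.75 | 0.50 |
| 1800 | 70 | 0.73 | 0.50 |
| 2000 | 80 | 0.72 | 0.50 |

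At 44 events the apparent AUC is 0.79 and at 84 it is 0.71. At least one null marker reaches p < 0.05 in about 93 to 95% of runs.

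**5. One marker at a time, no correction.** Expected false positives: 50 × 0.05 = 2.5. Chance of at least one: 1 − 0.95^50 = 0.92, taking the tests as independent.

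**6. Infected women only.** Ever infected by 18 months: A, (0.05 + 0.95 × 0.05 × 1.5) × 1800 = 218; B, (0.07 + 0.93 × 0.05 × 1.5) × 1800 = 252. With about 25 events this is 0.5 per marker, and an unpenalised null fit shows an apparent AUC of about 0.9.

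No count can be derived for Ct persistence: the only planning assumption is that untreated infection does not clear.

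**The case against.** The strongest reply is that the article is a condensed source and gives this analysis one clause. It does not say that the markers enter one unpenalised model, that an uncorrected AUC will be reported, or that a tool will come from this fit. Shrinkage, internal validation and multiplicity are matters that an analysis plan normally settles, and the analysis is labelled exploratory. All of that is fair. A reader might infer that the regression is bound to appear predictive; the document does not support that. If the question were answered by a single global likelihood-ratio test, false positives would be only mildly inflated, at about 5 to 9% for a nominal 5%.

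Two further inferences go too far. One is that there is never more than one event per marker: the endpoint runs to 24 months and final visits fall between months 18 and 24, so the ratio may reach 1.7. The other is that the whole control arm is simply the wrong population: Secondary objectives includes susceptibility to Ct, which needs uninfected women, and restriction alone would worsen the overfitting (step 6).

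What stands is that both natural ways of carrying out the stated analysis mislead if nothing is added. The unqualified claim in the abstract is also in the document itself and does not fit its planning figures, whatever an analysis plan may add.

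**Conclusion.** The concern holds in a limited form. The planning figures give 0.9 to 1.7 control-arm PID events per marker, about half of them from Ct infection. That is too few to support identification of at-risk women by ordinary logistic regression on 50 markers. The false appearance is an AUC of about 0.72 to 0.77 for an unpenalised joint fit, or a 92% chance of at least one spurious marker for uncorrected single tests.

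This rests on a reconstructed control risk, on reading the scenario rates as yearly, on 10% attrition, and on independent markers in the simulation. The event count is low under every reading tried, so the conclusion does not depend on which is right. It should be corrected, but it is a secondary, exploratory matter: the primary relative risk and the sample size are untouched.

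**What to change.** - **Prediction:** use ridge or LASSO logistic regression, with all fitting and tuning inside cross-validation or bootstrap. Report the optimism-corrected AUC and calibration, and state the expected event count.
- **Single markers:** report associations with false-discovery-rate control.
- **Population:** analyse Ct persistence, and progression to PID, among women with at least one Ct-positive swab, always with the penalised model. Keep any PID analysis of the whole control arm as a separate susceptibility question.
- **Wording:** recast the abstract's claim about identifying women at risk, and the tool aim in Expected results, as hypothesis-generating and in need of external validation.

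A ready-made one-degree-of-freedom score from the existing panel is not an evident shortcut: its weights are not in the document, and the panel was validated for tubal factor infertility.

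The cost is some wording and a little more analysis work with routine software. Apparent performance will be lower. No new data, visits or participants are needed.
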